
Acupuncture is a treatment that was previously shown to reduce diarrhea for irritable bowel syndrome patients^[17,18]^ along with a reduction in gastroparesis syndrome.^[19,20]^ Acupuncture was also shown the ability to regulate gastrointestinal mobility through different physiological pathways.^[21]^ Acupuncture decreased the fasting glucagon-like peptide-1 levels in an animal model^[22]^ and also showed the ability to decrease insulin and glucagon levels.^[23]^ In oncological patients, acupuncture reduced chemotherapy-related abdominal pain, nausea, vomiting, and diarrhea with good safety.^[24–26]^ We have chosen to compare acupuncture to shallow needling on sham non-acupoint in order to generate a reliable placebo effect that resembles acupuncture intervention processes.

There are no previous studies that have examined the direct use of acupuncture on dumping syndrome. The goal of this single-blind randomized control trial is to investigate the effect of acupuncture on dumping syndrome in esophagus cancer patients with jejunostomy tube feeding. We hypothesize that acupuncture will be superior to sham acupuncture in regulating dumping syndrome.

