### 2.14. Sample size calculation

Since no previous similar study was conducted, the sample size was determined via the G*Power version 3.1.9.4 software calculation, based on a large effect for a two-tailed *t* test. The calculation showed that a total of 26 patients were needed. However, to account for a 15% patient drop-out expected frequency. For 80% power with an effect size of 0.8, a total of 60 patients were required, with 30 patients in each group.

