### 2.16. Statistical analysis

The statistical analysis for all measurements will analyze changes from baseline and changes over time. Categorical data will be presented as a percentage (n %), while continuous data will be presented as mean ± standard deviation. For changes from baseline the paired *t* test will be used. The independent *t* test or the Mann–Whitney *U* test will analyze continuous variables depending on applicability, and the Chi-square test or Fisher’s exact test (as appropriate) will be used for categorical variables. For repeat measurements data the repeat measures ANOVA will be used. The IBM SPSS Statistics version 22.0 (SPSS Inc, Chicago, IL) will be used for data analysis, and significance will be determined at a *P* value < .05. If applicable, a subgroup analysis will be done on tumor stage, age, BMI, dumping syndrome status at baseline and dumping syndrome type. If there are any missing data, they will be imputed using multiple imputations (if applicable).

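### Change from baseline is assigned to a within-arm paired t test; the between-arm tests that are named are not tied to change and do not use the collected baseline

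*Protocol article*

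**What the plan says.** Section 2.16 of the protocol article opens with the scope: "The statistical analysis for all measurements will analyze changes from baseline and changes over time". It then gives three rules for continuous data:

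- Change: "For changes from baseline the paired *t* test will be used".
- Continuous variables in general: "The independent *t* test or the Mann–Whitney *U* test will analyze continuous variables depending on applicability".
- Repeated data: "For repeat measurements data the repeat measures ANOVA will be used".

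The second rule does not say whether it applies to change scores or to values at a visit, or which visit. The third mentions no group factor, group-by-time term or baseline covariate. The threshold is that "significance will be determined at a *P* value < .05".

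The question the trial asks is between arms. Section 1 says: "We hypothesize that acupuncture will be superior to sham acupuncture in regulating dumping syndrome". Section 2.14 sizes the trial "based on a large effect for a two-tailed *t* test" and concludes: "For 80% power with an effect size of 0.8, a total of 60 patients were required, with 30 patients in each group". Section 2.12 schedules weight, BMI and grip strength weekly, and Sigstad's score and the Arts questionnaire at baseline, week 3 and week 6.

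**The concern.** The only test attached to change from baseline cannot answer the superiority question. A paired t test in the acupuncture arm asks whether that arm changed; a second one in the sham arm asks the same of sham. A significant result in one arm and not in the other is not a test of the difference between them.

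A shared change is plausible here. Section 2.3 requires patients to have had a feeding jejunostomy and to have chemoradiation planned, and either could shift weight and symptoms in both arms whatever acupuncture does. When treatment starts relative to baseline is not given, so this remains an assumption.

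The second part is efficiency. Baseline values are collected for all the main outcomes, yet no named between-arm test uses them as a covariate. This matters most for weight: the Discussion says that if few patients develop dumping syndrome, weight and BMI become the focus, and for weight an unadjusted comparison of final values carries all of the between-patient spread. Randomization is simple and unstratified (Section 2.7), so chance baseline imbalance is possible with 60 patients.

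**Working it through.** **Step 1. Which test does the sample size assume?** Inputs from Sections 2.14 and 2.16: d = 0.8, two-sided alpha 0.05, 80% power, 15% drop-out.

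- Two-sample t test (noncentral t): 25.5, so 26 per arm and 52 in total. 52 × 1.15 = 59.8, so 60. The stated 60 is reproduced.
- Paired t test with a standardized change of 0.8: 14.3, so 15 patients. This does not lead to 60.

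The trial was therefore sized for a between-arm comparison, not for the test assigned to change.

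**Step 2. What would comparing two paired tests do?** Suppose there is no treatment difference, 30 patients per arm, and the same true change in both arms, expressed as dz (mean change divided by the SD of change). The document gives no value; 0 to 0.8 is assumed. Let p be the chance that the paired t test is significant in one arm. The arms are independent, so:

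- only the acupuncture arm significant: p(1 − p)
- exactly one arm significant: 2p(1 − p)

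| dz | p | only acupuncture | exactly one arm |
|---|---|---|---|
| 0 | 0.050 | 4.8% | 9.5% |
| 0.2 | 0.185 | 15.1% | 30.2% |
| 0.37 | 0.500 | 25.0% | 50.0% |
| 0.5 | 0.754 | 18.6% | 37.1% |
| 0.8 | 0.988 | 1.1% | 2.3% |

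The chance of an apparent acupuncture-only result peaks at 25% and falls away on both sides.

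**Step 3. What does baseline adjustment gain over the between-arm alternatives?** Take 26 evaluable per arm and d = 0.8 on the final value. The correlation r between baseline and final value is not given; 0.3 to 0.7 is assumed. Relative to the final-value test, the variance is 2(1 − r) for a change score and 1 − r² for ANCOVA, so the effective d is 0.8 divided by the square root of that factor.

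| r | final value | change score | ANCOVA |
|---|---|---|---|
| 0.3 | 80.7% | 66.7% | 84.3% |
| 0.5 | 80.7% | 80.7% | 90.4% |
| 0.7 | 80.7% | 95.5% | 97.7% |

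The gain over the final-value test is modest at 0.3 and large at 0.7. ANCOVA is the most powerful of the three in every row.

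**Step 4. When is the gain over a change score small?** The variance of ANCOVA relative to the change score is (1 − r²) / [2(1 − r)] = (1 + r)/2, which approaches 1 as r rises. If d = 0.8 is placed on the change scale with 51 evaluable (60 × 0.85, that is 25.5 per arm), the change-score test has 80% power. ANCOVA has 90%, 86%, 82% and 81% at r = 0.5, 0.7, 0.9 and 0.95. For an outcome such as weight, where r is likely to be high, most of the benefit comes from comparing change between arms at all; the covariate adds little more.

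**The case against.** The strongest reply is that between-arm tests are planned. The independent t or Mann–Whitney test and repeated-measures ANOVA stand in the same section, the hypothesis is comparative, and the sample size is that of a two-sample test. The section can be read as paired tests within arms, independent tests between arms and ANOVA over time. A group-by-time interaction in that ANOVA would be a valid comparison of change; with two time points its F equals the square of the t statistic on change scores. All of this stands. A reader might infer that no between-arm comparison is planned, or that efficacy will be judged by setting two within-arm p-values side by side. The article says neither.

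A reader might also infer that the plan has very low power for weight. In a simulation with assumed inputs (26 per arm, 2 kg effect by week 6, between-patient SD 3 kg, slope SD 0.35 kg per week, residual SD 0.8 kg), a t test on final weight has about 47% power and the ANOVA arm main effect about 20%. Those are the least favourable readings of the section, and the article commits to neither. With the same inputs a between-arm t test on change reaches about 84%, ANCOVA about 83% and the arm-by-week interaction about 86%, so a favourable reading of the plan loses nothing against ANCOVA.

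Finally, covariates and contrasts are often left to an SAP, which is not shown here, and a journal article condenses. That limits the weight of the missing covariate. It does not remove the point about change, because there the article does fix a test, and it is a within-arm one that a later SAP would have to override.

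**Conclusion.** The point holds in a limited form. Change from baseline, a declared target for all measurements, is tied to a test that does not compare the arms. The between-arm tests that are named are not tied to change, to a visit or to the baseline value. Which comparison carries the efficacy conclusion is therefore open, and the candidates can differ widely in power.

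The 1% to 25% range applies only if the paired tests were taken as evidence of efficacy, and it depends on an assumed common change of 0 to 0.8 SD. The power figures rest on assumed correlations and on d = 0.8. The gain from adjustment can be large against unadjusted final values and is small against a between-arm test of change when the correlation is high.

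This should be fixed. It is a free improvement in precision and clarity, not an error that prevents the trial from answering its question.

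**What to change.** State in Section 2.16, or in the SAP with an explicit note that it replaces the paired-test sentence, that the treatment effect is the between-arm difference at week 6 with the baseline value as covariate, reported with a 95% CI. Use either ANCOVA on the week-6 value, or a mixed model over visits with an arm-by-week term and a week-6 contrast. Apply it to body weight, Sigstad's score, the Arts score and grip strength. Keep the paired t tests as a description of change within each arm, and say that they will not be used to infer a difference between arms.

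The cost is a few sentences. Baseline is already collected, the models run in the SPSS version already named, and the 60 patients need not increase.

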### 2.8. Interventions

A sum of 60 patients from the China medical university will be divided into 2 groups. In both the INT group and CON group, A qualified acupuncture doctor with at least 2 years of clinical experience will provide the intervention sessions on both groups. The acupuncture frequency will be 2 times a week for 6 weeks in both groups. Both groups will also receive routine Western medicine treatments.

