### 2.12. Outcome measures

Main outcome measurements are: body weight, BMI (will be measured weekly) dumping syndrome questioners: the Sigstad’s score in order to determine the diagnosis of dumping syndrome and the Arts’ dumping questionnaire in order to assess early or late dumping syndrome (will be measured on the baseline, week 3, week 6) (see Figure S1, Supplemental Digital Content, http://links.lww.com/MD/J34 for the Sigstad’s score and Figure S2, Supplemental Digital Content, http://links.lww.com/MD/J35 for the Arts’ dumping questionnaire).

The secondary outcomes are: muscle grip strength test (measured weekly in kg) (by electronic hand grip test model EH101 manufactured by “CAMRY,” China), blood test: Complete Blood Count, kidney and electrolytes (measured as adjuvant adjuvant concurrent chemoradiation therapy schedule), pre-albumin, albumin level, glucose blood levels, inflammation data including Erythrocyte Sedimentation Rate and C-reactive protein (measured at baseline and on week 6). Total Intensive care unit stay, total hospital stay, and total mechanical ventilation in days will be measured 6 months after inclusion. Mortality will be measured at 3 months, 6 months. Medical charts and drug use will also be measured (Fig. 4). All measurements will be measured by nurses and doctors in the department that are blind to the study group allocation.

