Limitations of the study include a specific Taiwanese population and cannot be generalized to other populations. This study is also only a single-center study. The study protocol could not apply a double-blind design due to the type of intervention (manual acupuncture). The study will investigate the role of acupuncture in the prevention of dumping syndrome and malnourishment, the study does not require a positive Sigstad’s score to verify dumping syndrome as a condition for inclusion, therefore it is possible that the number of patients that will develop dumping syndrome could be low, in this case, the study will focus on body weight and BMI as the main outcomes to assess the prevention of malnourishment. The study did not specify the cancer stage in the inclusion criteria. High mortality rates in Esophagus cancer might impair the completeness of the data and can increase the levels of missing data.

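### Repeated-measures ANOVA, with imputation that is conditional and not tied to it, suits weekly body weight badly in a trial that expects deaths; a baseline-adjusted mixed model is a cheap improvement

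*Protocol article*

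**What the plan says.** Section 2.12 lists the main outcomes as "body weight, BMI (will be measured weekly") together with two dumping questionnaires, which "will be measured on the baseline, week 3, week 6". Treatment lasts six weeks (section 2.8: "The acupuncture frequency will be 2 times a week for 6 weeks in both groups"). Section 2.16 sets the method for such data: "For repeat measurements data the repeat measures ANOVA will be used". The same section adds: "If there are any missing data, they will be imputed using multiple imputations (if applicable").

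The limitations paragraph of section 3 makes weight and BMI the focus if dumping syndrome turns out to be uncommon. It also warns: "High mortality rates in Esophagus cancer might impair the completeness of the data and can increase the levels of missing data". Section 2.14 sets the sample size "to account for a 15% patient drop-out expected frequency" and concludes: "For 80% power with an effect size of 0.8, a total of 60 patients were required, with 30 patients in each group".

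**The concern.** Classical repeated-measures ANOVA works on patients with a value at every visit. The protocol applies it to outcomes with many visits, in a population where it expects deaths to leave gaps. The stated remedy leaves three things open:

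- Imputation is conditional. If it is judged not applicable, the analysis falls back to complete rows.
- Nothing says how imputed data feed the ANOVA, or which quantity is pooled.
- The wording covers all missing data, so read literally it would impute body weights for patients who have died.

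The output is also awkward. An omnibus F test over all visits does not give the number a reader wants, which is the difference between arms at the end of treatment, adjusted for starting weight. The ANOVA's group term averages over visits and carries the full spread of body weight between patients. At stake is the clarity and efficiency of the result on the outcome the trial falls back on.

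**Working it through.** **1. The plan's own figure.** Inputs from sections 2.14 and 2.16: d = 0.8, two-sided alpha 0.05, power 80%, drop-out 15%. The noncentral t distribution gives 26 per arm (power 80.7%). Inflating, 26 × 1.15 = 29.9, so 30 per arm and 60 in total, as stated; 26/0.85 = 30.6 would give 31 per arm. The 26 must therefore be per arm, although section 2.14 calls it a total (13 per arm has 49.9% power). That is a separate wording matter.

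**2. Power if only complete patients are used.** Complete patients per arm = 30 × (1 − drop-out) × (1 − m)^6, where m is the share of visits missed each week over and above drop-out. The protocol gives no value for m, so a range is shown. Power is for a t test at d = 0.8.

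| Drop-out | m | Complete per arm | Power |
|---|---|---|---|
| 0% | 0% | 30 | 86.1% |
| 15% | 0% | 25.5 | 80.0% |
| 15% | 2% | 22.6 | 74.8% |
| 15% | 5% | 18.7 | 66.4% |
| 30% | 0% | 21 | 71.6% |

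The planned drop-out is already paid for. Power falls below plan only with further loss and no imputation.

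**3. Bias if imputation is not done.** Assumptions: true week-6 difference 1.8 kg (losses of 0.3 and 0.6 kg per week over six weeks), and drop-out more likely after greater observed weight loss. The figures are for the week-6 difference, since the ANOVA itself gives no such estimate.

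- About 15% drop-out: complete cases give 1.66 to 1.47 kg, a shortfall of 8% (1 − 1.664/1.8) to 18% (1 − 1.471/1.8).
- About 30% drop-out: 1.56 to 1.29 kg, a shortfall of 13% to 28%.
- Imputation within arm in the same scenarios: 1.79 to 1.81 kg, so the bias goes.

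**4. Sphericity.** The protocol gives no covariance, so several are assumed, with 7 visits (baseline plus six weekly, an inference from the schedule) and 25 patients per arm. Type I error of the group-by-time F test:

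| Covariance | Epsilon | Uncorrected | Greenhouse-Geisser |
|---|---|---|---|
| Compound symmetry | 1.00 | 5.1% | 4.2% |
| Random walk plus error | 0.65 | 7.4% | 4.7% |
| AR(1), 0.7 | 0.58 | 8.6% | 4.8% |
| AR(1), 0.9 | 0.44 | 10.1% | 4.6% |
| Random slopes | 0.26 | 12.1% | 4.7% |

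**5. The group main effect.** Assumptions: baseline SD 10 kg, slope SD 0.383 kg per week, residual SD 0.7 kg, and a true week-6 difference of 2 kg growing linearly from zero. The SD of six-week change is √(36 × 0.383² + 2 × 0.7²) = 2.5 kg, so d is about 0.8.

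- Arm difference in the seven-visit average: 2 × (0 + 1 + … + 6)/(6 × 7) = 1.0 kg.
- SD of a patient's average: √(10² + (3 × 0.383)² + 0.7²/7) = 10.07 kg.
- Standard error: 10.07 × √(2/30) = 2.60 kg, so the noncentrality is 0.38.
- Power: 6.7% by this formula, about 6% by simulation.

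Under the same assumptions with full data, the corrected group-by-time test has about 87% power and a week-6 comparison adjusted for baseline about 86%. With 15% drop-out, the complete-case interaction test keeps about 81% to 82%, against about 83% for a likelihood analysis with known covariance.

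**The case against.** The strongest reply is that the plan does address missing data. If imputation is carried out, most of the loss in steps 2 and 3 disappears. That stands. A reader might infer that the trial will certainly discard incomplete patients and end with power near 66% to 68%. The documents do not support that: it needs an undocumented 5% of missed visits each week and no imputation. Nor is imputation incompatible with an omnibus test, since multi-parameter pooling rules exist. The protocol merely does not connect the two.

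A reader might also infer that false positives will be inflated. The protocol neither makes nor excludes a sphericity correction. Such a correction is routine, can sit in an analysis plan, and restores the error rate to about 4% to 5%.

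Lastly, section 2.16 speaks of change from baseline and over time, which points to the interaction and not the group main effect, and it names an independent t test that could compare arms at one visit. The low power of the main effect therefore matters only if that term is read. What remains is that no term or week-6 contrast is named as the effect estimate.

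**Conclusion.** The point holds as a cheap improvement. The named method fits poorly with the trial's own expectation of deaths and gaps. The imputation meant to repair it is conditional, unconnected to the ANOVA and, as worded, reaches past death. No single baseline-adjusted week-6 difference results.

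The size is modest on documented inputs: at 15% drop-out, power stays at about 80%, and the gain in power from a mixed model is a point or two. The larger harms are conditional. Bias of 8% to 28% towards no effect requires outcome-dependent drop-out without imputation. Type I error of 7% to 12% requires an uncorrected test on non-spherical data. All variances, drop-out mechanisms and visit-level missing rates are assumptions, because the protocol gives none.

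**What to change.** Replace the ANOVA sentence in section 2.16 with: weekly body weight and BMI, and the other outcomes measured repeatedly, will be analysed by a linear mixed model for repeated measures on all observed post-baseline values. Terms are arm, visit, arm-by-visit and the baseline value as covariate. Covariance is unstructured, with a named fallback if the model does not converge. The effect estimate is the between-arm difference at week 6 with its 95% CI.

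Keep multiple imputation as a sensitivity analysis, state that values after death are not imputed, and report deaths by arm beside the result. That last step is still needed, because a mixed model does not by itself say how to interpret weight in patients who have died.

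The cost is wording, slightly more analysis work and a covariance structure fixed in advance. No new data or patients are needed.

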### 2.17. Dissemination

After study completion, the study results will be published in a medical journal.

## 3. Discussion

Dumping syndrome is often a side effect of digestive system physical alterations such as surgeries. The most common are esophageal, gastric, or bariatric surgeries.^[28]^ The rapid movement of hyperosmolar chyme leads to gastrointestinal and vasomotor symptoms.^[14]^ Dumping syndrome can lead to significant weight loss that can be resulted in hospitalization for hypoglycemia. It is especially an issue for advanced esophagus cancer patients as their high risk of malnourishment and can contribute to the patient’s extremely low 5 years survival rate.^[5,29]^

Although there is no previous study that investigated the effect of acupuncture on dumping syndrome, acupuncture showed great potential in alleviating digestive system symptoms. Acupuncture was found to be superior to conventional treatments for diarrhea in a meta-analysis of 17 studies on irritable bowel syndrome patients.^[30]^ The acupoint PC6 (Neiguan) effect on nausea was shown to be beneficial in a Cochrane meta-analysis of 59 studies, although the level of evidence was low.^[31]^ A meta-analysis of 20 studies found acupuncture to be superior to placebo and usual care in postoperative nausea and vomiting.^[32]^ Acupoint stimulation is also effective for postoperative nausea and vomiting after general anesthesia.^[33]^ For postoperative gastroparesis syndrome, a meta-analysis found that both acupuncture and acupuncture combined with medication showed a significant effect compared to the control, however, the level of evidence was low.^[19]^ In a clinical trial investigating acupuncture for patients after postoperative laparoscopic common bile duct exploration, the acupoints ST36 (Zusanli), ST37 (Shangjuxu), and ST39 (Xiajuxu) with early Enteral Nutrition (EN) significantly improve the patient’s outcomes in digestive symptoms, had fewer complications, and a shorter hospital stay.^[34]^ In our previous clinical trial, acupuncture on the digestion specific points reduce postoperative feeding intolerance and reduce the use of the prokinetic drug in critically ill oral cancer patients.^[27]^ Acupuncture showed to be as effective as oral administration of Mosapride for patients with chronic functional constipation.^[35]^ A review conducted by Li et al on both animals and humans revealed the ability of acupuncture to regulate gastrointestinal function. The review showed that the acupoints ST36 (Zusanli), PC6 (Neiguan), and LI4 (Hegu) have the ability to increase or decrease gastric and colonic motility. The motility changes appear to be regulated depending on the patient’s condition. The review also found that the regulating effect of the acupoint ST36 (Zusanli) is often occurring through the vagal pathway, in cases where the ST36 (Zusanli) decreased colonic motility, it was done through Oxytocin expression.^[36]^ The array of evidence justifies the use of acupuncture for digestion-related conditions. Our study includes the acupoints ST36 (Zusanli), ST37 (Shangjuxu), ST39 (Xiajuxu), PC6 (Neiguan), and LI4 (Hegu) that were mentioned in the above studies, and in our intervention group acupuncture protocol.

In general, Acupuncture in cancer patients is considered a supplementary treatment that can contribute to the patient’s overall recovery, and reduce chemotherapy and radiation therapy side effects, but not a replacement of Western medicine therapies. A small meta-analysis on the efficacy of acupuncture in chemotherapy-induced peripheral neuropathy conducted by Chien et al^[37]^ found an effective ability of acupuncture to reduce peripheral neuropathy pain and functional limitation. Zhang et al^[38]^ conducted a meta-analysis including 10 studies on cancer-related fatigue. The meta-analysis found acupuncture to be an effective treatment for cancer-related fatigue. Jang et al^[39]^ found similar effects in an updated systematic review and meta-analysis on cancer-related fatigue for cancer survivors. Chiu et al^[40]^ in a systematic review and meta-analysis on cancer-related pain that included 29 studies found that acupuncture is effective in malignancy and surgical related analgesia and recommended that acupuncture can be combined with routine treatments for analgesia in cancer patients. A small meta-analysis found that acupuncture is also a beneficial treatment for cancer patients suffering from hiccups, however, the level of evidence was low.^[41]^ Ni et al^[42]^ conducted a meta-analysis on acupuncture for radiation-induced xerostomia and found some level of effectiveness in reducing xerostomia following acupuncture, although a low level of evidence.

Specifically in esophagus cancer patients, acupuncture was investigated in a study conducted by Tang et al on the application of acupuncture anesthesia in operation for carcinoma of the esophagus found a good analgesic effect during the surgery following acupuncture.^[43]^ Li et al^[44]^ used porous nano-sensing acupuncture for anesthesia in 30 esophageal cancer after one-lung ventilation thoracotomy and found a significant improvement in cognitive function, reduced level of inflammatory factors, and improved therapeutic effect. A small systematic review on acupuncture effect for radiation-induced xerostomia in patients suffering from head and neck cancer did not find any superior effect of acupuncture over the control but showed good safety for acupuncture on head and neck cancer patients.^[45]^ The effect of acupuncture on the esophageal organ in non-cancer patients is demonstrated in a study on the acupoint ST36 (Zusanli) that was shown to significantly reduce the lower esophageal sphincter resting pressure.^[46]^ In a case report, acupuncture was effective for oropharyngeal dysphagia and esophageal motility disorder.^[47]^ Overall acupuncture’s effect on esophageal cancer patients was not well investigated and more research on this intervention is needed.

This research will investigate a possible cooperation and integration approach of both Western and Chinese medicine in esophagus cancer treatment. In this integration, each treatment method focuses on its strength, western medicine in tumor treatment, and Chinese medicine in digestion symptoms in order to improve the patient’s condition and quality of life. This research will shed more light on the effectiveness of acupuncture as an intervention for both esophagus cancer patients and dumping syndrome. In the case that the study findings will be in favor of acupuncture, it will provide a valuable, low-cost supportive therapeutic option for advanced esophagus cancer patients with dumping syndrome.

Limitations of the study include a specific Taiwanese population and cannot be generalized to other populations. This study is also only a single-center study. The study protocol could not apply a double-blind design due to the type of intervention (manual acupuncture). The study will investigate the role of acupuncture in the prevention of dumping syndrome and malnourishment, the study does not require a positive Sigstad’s score to verify dumping syndrome as a condition for inclusion, therefore it is possible that the number of patients that will develop dumping syndrome could be low, in this case, the study will focus on body weight and BMI as the main outcomes to assess the prevention of malnourishment. The study did not specify the cancer stage in the inclusion criteria. High mortality rates in Esophagus cancer might impair the completeness of the data and can increase the levels of missing data.
